## Outcomes

### Implementation outcome—fidelity

Fidelity is defined as the degree to which programs [in principle evidence-based practices] are implemented as intended. It is demonstrated that the fidelity with which an intervention is implemented affects how well it succeeds, e.g., impacts on the relationship between the intervention and its intended outcomes [54]. To our knowledge, only a few previous ACP-studies have assessed fidelity, but relating fidelity solely to the intervention or the degree to which an intervention is delivered as intended (i.e. the quality of ACP) [55, 56]. This refers to a narrower conception of the term fidelity [54]. To capture both the complexity of ACP as an intervention and the complexity of the implementation process aiming to put ACP into routine practice, we developed a novel, broader and more comprehensive fidelity scale, including three subscales measuring:The current level of implementation of the selected recommendations, i.e. adherence to the intervention (quality of ACP)The penetration rate, defined as the percentage of consumers who are offered and receive ACP as an evidence-based practice, as measured against the total number of consumers who could benefit from the evidence-based practice [57]The implementation process, by measuring the level and quality of selected implementation strategies and implementation interventions

We used Bond’s standardized methodology for developing and validating fidelity scales [58], and selected recommendations from national and international guidelines clustering them into key items [14, 16, 59]. The scale consists of 22 items that are scored from 1 to 5, where 1 equals poor implementation and 5 equals full implementation of ACP. The development and details of the scale will be published. The psychometric properties of the scale will be assessed, and we will optimize and ensure its usefulness and availability to other researchers and the health care services after the project period.

#### Data collection

We defined baseline as the situation before the start of the intervention, and the baseline fidelity measurements were conducted from May to August 2022. The participating hospital units were randomized to the intervention- or control arm after the baseline fidelity measurement in August 2022. The implementation period started with kick-off on Oct 25th, 2022, and will continue for approximately 18 months (when the inclusion for the triadic sub-study is completed, and before the last measurement of fidelity). Fidelity measurements in the intervention arm will be at baseline, at 7–10 months after the start of the intervention (May to August 2023) and at 18 months (April 2024). Fidelity measurements in the control arm will be at baseline and at 18 months. The second fidelity measurement is not done in the control group due to resource considerations, and to avoid influencing clinical activity in the control arm.

The fidelity scores at each unit will be based on a) interviews with leaders, b) interviews with resource persons, c) interviews with physicians, d) interviews with nurses, e) written material (e.g., information brochures or clinical procedures) and f) existing routine data (number of patients eligible for/offered/received ACP). Seven of the project members participate in the data collection, forming teams of two people visiting each site. Based on the interviews and available information, the two researchers will, at the end of the visit, score fidelity individually, and subsequently discuss possible discrepancies and decide on a consensus score.

#### Outcomes and data analysis

The fidelity measurements will provide an answer to the first primary outcome of this study, by comparing change in fidelity from baseline to 18 months in the intervention arm versus the control arm. We will report changes in total fidelity, in sub-scales and in relevant single items. The baseline fidelity scores provide data on the current level of implementation of ACP, thereby answering the first of the secondary objectives. Baseline data will be analyzed using descriptive statistics, including means, ranges, standard deviations (SD), and number of sites achieving low, adequate and full implementation of the various items. Interrater reliability will be investigated by calculating the ICC for total mean fidelity and for each item, using a one-way random effects analysis of variance model for agreement between two assessors. Difference between experimental and control arms in change on the ACP scale (primary outcome) from baseline to 18 months, will be assessed by an Independent samples t-test. The results will be presented as mean difference with corresponding 95% confidence interval (CI), p-value and effect size (Cohen’s d) with 95% CI. The differences between the experimental and control arms in change on the ACP scale and sub-scales will be assessed by linear mixed models with random intercepts for clusters. All analyses will be performed in SPSS, STATA or R.

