The units were sorted from one to 12 according to the number of geriatric beds and then stratified into three strata: four clusters with 16 to 23 beds, six clusters with 6 to 10 beds and two clusters with 4 and 5 beds respectively. In each block, the clusters were randomized to either the intervention or the control arm with an allocation ratio of 1:1. An independent professor in epidemiology performed the allocation using the Microsoft Excel RAND-function, only knowing the numbers of the clusters. The randomization was performed to achieve a balance in unit types in the intervention and control arm and a similar size of the two arms including a similar number of admitted patients filling the inclusion criteria. All hospitals are located in cities or towns. The purpose of the stratification was primarily to achieve a balance in the number of patients and next of kin between the two arms, and secondly to include units of various sizes in both.

The study has primary outcomes for the implementation and for the clinical effectiveness. The primary outcome for the implementation outcome sub-study is the differences in fidelity changes between the arms. The unit of analysis for the fidelity scores is the health care units or clusters. Fidelity is rated on 5-point scales (1 = poor fidelity, 5 = high fidelity). Based on previous research (mean difference 1.82 and average SD 0.80 after 18 months with implementation support), we have calculated that we need at least four clusters in each arm to show that implementation support gives a significant increase in fidelity, based on 5% two-tailed significance and 80% power. If the differences are smaller in our study, we will need a larger sample. Due to the possibility of unit drop-out during the project period and to secure sufficient power, we have included six units in the intervention arm and six in the control arm.

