#### Data analysis

Demographic and clinical data about the patients will be used to assess whether the patients in the control and intervention units are comparable. In addition, the participating units will collect basic and anonymous clinical information about all patients admitted to the units at shorter random time periods, to get more information about the participant units and to compare the included patients with all admitted patients.

Number and percentages of invitation to and participation in ACP for patients and next of kin will be calculated and compared between intervention and control group. The primary statistical analyses will be the difference in mean outcomes between participants in the intervention and the control group using linear mixed effects models. The random part of the model will consist of random intercept for patient or relative identification nested within centre. Missing data will be handled by multiple imputation using predictive means matching with 100 imputed data sets.

If the analyses show differences in the intervention and control arm, we will perform analyses to assess if higher fidelity score (higher levels of implementation) is associated with improved outcomes for patients, next of kin, and clinicians. For the secondary outcomes, we will compute average outcomes and SD for the intervention and the control group and use the t-test to determine if there is a significant difference between groups.

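### The primary fidelity t-test ignores the three bed-size strata used in the randomisation, so its interval is too wide and its test conservative if unit size relates to change in fidelity

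*Protocol article*

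**What the plan says.** Under 'Selection, allocation of clusters and sample size', the protocol article orders the units by number of geriatric beds. The grouping reads: "stratified into three strata: four clusters with 16 to 23 beds, six clusters with 6 to 10 beds". The third stratum holds the remaining pair of units, the smallest, of 4 and 5 beds. On allocation the section says: "In each block, the clusters were randomized to either the intervention or the control arm with an allocation ratio of 1:1". This gives splits of 2:2, 3:3 and 1:1. The same section says: "The purpose of the stratification was primarily to achieve a balance in the number of patients and next of kin between the two arms". Having units of various sizes in both arms was the second aim.

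The fidelity sample size rests on "mean difference 1.82 and average SD 0.80 after 18 months with implementation support", "based on 5% two-tailed significance and 80% power". The result is at least four clusters per arm. To allow for drop-out, "we have included six units in the intervention arm and six in the control arm".

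Under 'Outcomes and data analysis' for fidelity, the arm difference in change on the ACP scale, the primary outcome, "from baseline to 18 months, will be assessed by an Independent samples t-test". Linear mixed models with cluster intercepts are named as well, for the scale and its sub-scales, again without a stratum term.

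For the triadic sub-study, 'Data analysis' names linear mixed models and describes only their random part: "The random part of the model will consist of random intercept for patient or relative identification nested within centre". It does not list the fixed effects.

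**The concern.** Stratified allocation with exact balance takes differences between strata out of the arm contrast: each arm holds the same mix of large, middle and small units. An independent samples t-test does not use this. It puts all variation among the six units of an arm into the error term, including the variation between strata that can no longer disturb the comparison. The estimate itself is unaffected while all 12 units remain. The standard error is too large to the extent that strata differ in the outcome.

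Two conditions limit the point. The outcome is a change score, so a stable size effect on the level of fidelity cancels, and only a relation between size and change counts. The consequence is also one-sided: precision and power are lost, but no false positives are created.

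At stake is the width of the interval reported for a primary outcome measured on 12 units, and the power to detect an effect smaller than planned.

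**Working it through.** **Inputs from the protocol article.** Strata of 4, 6 and 2 units, balanced 1:1; six units per arm; planned difference 1.82; SD 0.80; two-sided 5%.

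**Assumptions.** 0.80 is taken as the SD of unit-level change within an arm. The strata explain a share f of that variance, through a linear effect across the three size groups. The documents give no value for f, so 0 to 30% is shown.

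**The plan's own figure.** n per arm = 2 × [0.80 × (1.960 + 0.842) / 1.82]² = 3.03, rounded up to 4, so the stated figure reproduces. With six per arm and the t distribution on 10 df, power at 1.82 is 94%.

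**Standard errors.** The variance is 0.80² = 0.64, and the arm contrast has multiplier 2/6 = 1/3.

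- True variance of the contrast under stratified allocation: 0.64 × (1 − f) / 3.
- Mean pooled variance in the t-test: residual part 10 × 0.64 × (1 − f) plus stratum part 12 × 0.64 × f, divided by 10 df. This equals 0.64 × (1 + 0.2f).
- At f = 0.3 the true SE is √(0.64 × 0.7 / 3) = 0.386. The t-test works with about √(0.64 × 1.06 / 3) = 0.475.
- Critical values are 2.228 on 10 df without strata and 2.306 on 8 df with strata.

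**Simulation.** 12 unit-level values in the 4/6/2 layout; the t-test on 10 df is compared with a linear model on arm plus stratum on 8 df. The stratum-adjusted test stays at about 5% type I error throughout.

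| Share f | True type I error, t-test | Mean 95% half-width, t-test | Mean 95% half-width, adjusted |
|---|---|---|---|
| 0% | 5.0% | 1.00 | 1.03 |
| 10% | 3.9% | 1.01 | 0.98 |
| 20% | 2.8% | 1.03 | 0.92 |
| 30% | 1.9% | 1.04 | 0.86 |

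The adjusted interval becomes the narrower one from about f = 5%.

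| True difference | Share f | Power, t-test | Power, adjusted |
|---|---|---|---|
| 1.82 | 0% | 94% | 93% |
| 1.82 | 30% | 96% | 98% |
| 1.0 | 0% | 50% | 48% |
| 1.0 | 30% | 47% | 62% |

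**Permutation reference set.** C(4,2) × C(6,3) × C(2,1) = 6 × 20 × 2 = 240 allocations. The smallest possible two-sided p-value is 2/240 = 0.008, so a 5% test is feasible.

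**The case against.** The strongest reply is that nothing in the documents shows bed size predicting change in fidelity. The 'Setting' section says that size partly reflects how geriatric services are organised and prioritised, but this says nothing about response to implementation support. The strata were chosen mainly to balance participant numbers. If size is unrelated to change, the t-test is exact and slightly more powerful. At the planned effect, power is ample either way, and any error is towards caution. All of this stands, and it limits the size of the point. It does not remove it: the effect on the standard error follows from the restricted allocation whatever its motive, and the article itself allows that differences may be smaller than planned.

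Drop-out is a second fair objection. The article anticipates it, and the smallest stratum has one unit per arm. If one of those two leaves, the other gives no information on the arm difference in an adjusted model.

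A reader might infer that the triadic primary analyses share the fault. The documents do not support that. The article gives only the random part of those models, and a stratum term would be a fixed effect, which a fuller plan may contain. Nor can those tests be called conservative, because no degrees of freedom are fixed. With a large-sample z test on 12 clusters of 22, simulated type I error is 7.9% if strata explain nothing and 5.8% if they explain 25% of the between-cluster variance, so such a test could be liberal.

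**Conclusion.** The point holds for the primary fidelity analysis. The named test cannot reflect the stratified allocation, so this is a stated choice and not a detail left open. Its cost depends on an unknown. It is nil if strata explain none of the variance in change. At 20 to 30% it is a true type I error of 2.8 to 1.9% and a mean half-width of 1.03 to 1.04 where 0.92 to 0.86 was available. Power is hardly touched at a difference of 1.82. At 1.0 with a 30% share, 15 points are lost (62% − 47%). These figures assume all 12 units retained, an SD of change of 0.80 and roughly normal unit-level changes.

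A reader might also infer bias or an inflated false-positive rate in the fidelity result. Neither follows: with all units retained the estimate is the same, and the error is towards caution. The change is worth making because it is cheap and because only 12 units carry this outcome. It does not threaten the trial's validity.

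**What to change.** Replace the t-test with a unit-level linear model of change in fidelity from baseline to 18 months on arm plus the three-level bed-size stratum, tested on 8 df. Report the adjusted difference with its 95% CI. As a check without distributional assumptions, add a permutation test over the 240 allocations that the randomisation could have produced. Do not fit stratum-by-arm terms, since the smallest stratum has one unit per arm. State in advance what happens to that stratum, and to the permutation set, if a unit drops out. Because the researchers are not blinded to allocation, date and record the change before the 18-month fidelity scores are compared by arm.

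The cost is 2 of 10 degrees of freedom: about 2 points of power at a difference of 1.0 if size is unrelated to change (50% to 48%), and a mean half-width of 1.03 in place of 1.00. No new data are needed.

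As a suggestion only, the triadic mixed models could name the stratum as a fixed effect. This should come together with small-sample degrees of freedom, because a stratum term tested against a large-sample cut-off would not control the error rate.

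### Cohen's d, reported beside the mean difference for the primary fidelity contrast, overstates the standardised effect by about 8% on average with six units per arm; Hedges' g would remove this

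*Protocol article*

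**What the plan says.** Under Implementation outcome—fidelity, Outcomes and data analysis, the between-arm difference in change from baseline to 18 months "will be assessed by an Independent samples t-test". The same paragraph then fixes the reporting: a mean difference with its 95% confidence interval, then "p-value and effect size (Cohen’s d) with 95% CI". The raw mean difference comes first and d is added to it. No small-sample correction is named.

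The section Selection, allocation of clusters and sample size supplies the numbers behind d. "The unit of analysis for the fidelity scores is the health care units or clusters", and "we have included six units in the intervention arm and six in the control arm". It also allows for units dropping out, without giving a rate. Its planning values are "mean difference 1.82 and average SD 0.80 after 18 months with implementation support", from which it derives a minimum of four clusters per arm, "based on 5% two-tailed significance and 80% power".

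**The concern.** Cohen's d divides the mean difference by an SD estimated from the same data. When few units supply that SD, its reciprocal is too large on average, so d is biased away from zero whatever the true effect. In a trial with hundreds of independent observations the bias is negligible. Here the analysis rests on 12 units.

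What is at stake is one reported figure for a primary outcome. The fidelity scale is new, so readers have no established sense of what one point on it means and may lean on the standardised figure when comparing this trial with others. A known, one-directional bias in that figure is worth removing when the correction is an exact constant.

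**Working it through.** **Inputs.** Six units per arm, the unit as unit of analysis, and an independent-samples t-test on change (all from the article). Pooled degrees of freedom: m = 6 + 6 − 2 = 10. Planning difference 1.82 and SD 0.80 (article). Assumptions: normal change scores, equal variances in the two arms, and a pooled SD as the standardiser. The dropout rate is not stated, so I take zero to two units lost per arm.

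**The plan's own figure.** Clusters per arm = 2 × [(1.960 + 0.842) / (1.82/0.80)]² = 2 × (2.802/2.275)² = 3.03, rounded up to 4. This reproduces the stated minimum of four. The point made here does not touch that calculation.

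**Bias of d.** For a true standardised effect δ,

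E(d) = δ / J(m), with J(m) = Γ(m/2) / [√(m/2) · Γ((m−1)/2)].

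At m = 10: J = Γ(5) / [√5 · Γ(4.5)] = 24 / (2.236 × 11.632) = 0.923, so E(d)/δ = 1.084.

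| Units analysed | m | J(m) | Average excess of d |
|---|---|---|---|
| 6 v 6 | 10 | 0.923 | 8.4% |
| 6 v 5 | 9 | 0.914 | 9.4% |
| 5 v 5 | 8 | 0.903 | 10.8% |
| 4 v 4 | 6 | 0.869 | 15.1% |

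**Simulation check** (400,000 trials of 6 v 6 at each true effect).

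| True effect | Mean excess of d | Sampling SD of d |
|---|---|---|
| 0.5 | 8.3% | 0.66 |
| 1.0 | 8.3% | 0.70 |
| 2.275 | 8.4% | 0.90 |

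After multiplication by J(10), the remaining bias was about 0.1% or less in each case. The simulated mean difference was also within 0.1% of its true value.

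**Illustration at the planning values.** If the SD of 0.80 applied to change scores, δ would be 1.82/0.80 = 2.275 and the expected d would be 2.275/0.9227 = 2.47, an excess of 0.19. That is 0.19/0.90 = 0.21 of the sampling SD. An observed d of 2.275 would have a noncentral-t 95% interval of 0.74 to 3.74 and a corrected value of 2.275 × 0.9227 = 2.10.

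**Unequal variances.** If the variance of change differed strongly between arms, the effective degrees of freedom would fall from 10 towards 5 and the excess would rise towards 19% (1/J(5) = 1.189). The figure of 8.4% is therefore the lower end in that respect.

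**The case against.** The strongest reply is that this is a reporting preference about a supplementary statistic. The unbiased mean difference is listed first, d carries its own confidence interval, and the excess is about a fifth of a standard error at the planning effect. The median of d is only about 3% too high. A journal article may also leave the exact variant of an effect size to a fuller plan.

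Most of this stands and sets the weight of the point. The last part does not remove it. The article positively names Cohen's d, so the point concerns a stated choice and not an absent detail. A wide interval is also no reason to keep a removable bias.

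A reader might infer three stronger things that the documents do not support:

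- **That the primary result rests on d.** It does not. The mean difference, its interval and the p-value come first and are unaffected.
- **That the sample-size section shows such inflation passing into later trials.** That section planned from a raw difference and an SD, not from a published d. A later trial that followed this practice would use figures that replacing d with g leaves unchanged.
- **That the trial should expect d to be 2.47 in place of 2.28.** The SD of 0.80 is described as an average after 18 months and is not said to be the SD of change scores. The pair of numbers is an illustration only.

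**Conclusion.** The point holds as a minor improvement. If d is computed without correction from a pooled SD, it will overstate the standardised fidelity effect by 8.4% on average with six units per arm, and by up to 15.1% if only four per arm remain. These figures assume normality and equal variances. They do not depend on the true effect or on the planning values. The primary test, its p-value, the raw estimate and the sample size are not in question.

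**What to change.** In Outcomes and data analysis, replace Cohen's d with: Hedges' g (d times the exact small-sample factor for the degrees of freedom analysed, 0.923 at 10) with a noncentral-t 95% confidence interval. If units drop out, the factor follows the remaining degrees of freedom, for example 0.903 at 5 v 5. The noncentral-t interval already refers to the true effect, so its limits should not be multiplied by the factor again. The mean difference with its interval stays first, as planned.

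The change takes a few words and needs no new data. The only downside is a slightly smaller reported effect size.

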### Clinical effectiveness – The triadic sub-study with patients, next of kin and clinicians

In this sub-study, we will assess and compare ACP relevant outcomes between the intervention arm and control arm. As described, we use a triadic approach, by recruiting each patient together with a close relative, and an attending clinician. This allows us to assess and compare the perspectives of all three stakeholders across the two study-arms. We aim to include at least 420 triads in total from the two arms. Each person in each “triad” will complete a questionnaire inspired by past ACP-, end-of-life- and shared decision-making studies and adapted to the Norwegian context and the current study. Paper questionnaires will be used for patients, the next of kin can choose between paper and digital questionnaires and digital questionnaires will be used for the clinicians. The patients will be offered assistance in filling out the questionnaire by a staff not involved in the treatment of the patient. The inclusion of participants will start approximately 13 months after the start of the intervention in the implementation arm.

